- Evidence for Grade  $\geq 2$  hemolysis has returned to baseline or Grade  $\leq 1$  severity (or, at the Investigator discretion, Grade  $\leq 2$  if not considered a safety risk for the patient)
- Non-hematologic toxicities have returned to baseline or Grade  $\leq 1$  severity (or, at the Investigator discretion, Grade  $\leq 2$  if not considered a safety risk for the patient)

Sections 12.1.3 through 12.1.11 detail specific guidelines for the management of common AEs. Other AEs should be managed per published guidelines and Investigator discretion if clearly due to cetuximab or pembrolizumab.

General instructions for dose modification and toxicity management guidelines for immune-related AEs (additional details are provided in Sections 12.1.3 through 12.1.11):

- Severe and life-threatening irAEs should be treated with IV corticosteroids followed by oral steroids. Other immunosuppressive treatment should begin if the irAEs are not controlled by corticosteroids.
- Study intervention must be permanently discontinued if the irAE does not resolve or the corticosteroid dose is not  $\leq 10$  mg/day within 12 weeks of the last study intervention treatment.
- The corticosteroid taper should begin when the irAE is  $\leq$  Grade 1 and continue at least 4 weeks.

- If pembrolizumab has been withheld, pembrolizumab may resume after the irAE decreases to  $\leq$  Grade 1 and the patient is receiving  $\leq 10$  mg/day oral prednisone or equivalent
- Pembrolizumab must be permanently discontinued for  $\geq$  Grade 3 neurologic toxicity,  $\geq$  Grade 2 myocarditis, confirmed Stevens-Johnson Syndrome/Toxic Epidermal Necrolysis/Drug Rash with Eosinophilia and Systemic Symptoms, and other grade 4 or recurrent grade 3 immune-related adverse events.

Patients with grade 4 hypertension must not receive further treatment with cetuximab.

If the toxicity is unlikely due to cetuximab or pembrolizumab, there should be a low threshold to attribute it to evorpaccept (ALX148) and the following guidelines should be used:

- Patients experiencing Grade 3 or 4 potentially treatment related toxicity or intolerable Grade 2 toxicity despite maximal supportive care should have their treatment (evorpaccept (ALX148), cetuximab, **and** pembrolizumab) interrupted. Appropriate follow-up assessments should be performed until adequate recovery occurs as assessed by the Investigator.

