| Grade 2 (Symptomatic; medical intervention indicated; limiting instrumental ADL)             | 
 
• Evorpaccept (ALX148) may continue at the discretion of the investigator per medical judgment.
 
• Withhold pembrolizumab and cetuximab.
 
• Refer patient to pulmonary and infectious disease specialists and consider bronchoscopy or BAL.
 
• If bronchoscopy is consistent with immune-related etiology, initiate treatment with 1–2 mg/kg/day oral prednisone or equivalent.
 
• If event improves to Grade 1 or better within 2 weeks, resume cetuximab (dose determined by institutional guidelines). May consider resuming pembrolizumab at fixed dose at discretion of investigator and medical monitor.a,b,c
 
• Permanently discontinue study treatments and contact Medical Monitor if event does not resolve to Grade 1 or better within 2 weeks (unless otherwise agreed between the Investigator and AGICC).a,b,c
 
• For recurrent events, treat as a Grade 3 or 4 event.
 
 |
| Grade 3 (Severe symptoms; limiting self care ADL; oxygen indicated)                          | 
 
• Hold evorpaccept (ALX148)
 
• Permanently discontinue pembrolizumab and cetuximab.
 
                                                                                                                                                                                                                                                                                                                                                                                                                                                                                                                                                                                                                                                                                                                                                                                                                                                                |

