| OR

Grade 4 (Life-threatening respiratory compromise; urgent intervention indicated (e.g., tracheotomy or intubation)) | 
 
• Refer patient to pulmonary and infectious disease specialists and consider bronchoscopy or BAL.
 
• If bronchoscopy is consistent with immune-related etiology, initiate treatment with 1–2 mg/kg/day oral prednisone or equivalent.
 
• If pulmonary event does not improve within 48 hr or worsens, consider adding an immunosuppressive agent (e.g., infliximab, cyclophosphamide, IV Ig, or mycophenolate mofetil ).
 
• If event resolves to Grade 1 or better, taper corticosteroids over <math>\geq 1</math> month.
 
• If event resolves to Grade 1 or better, evorpacept (ALX148) may be resumed at 1 dose level lower if deemed appropriate by the Investigator and medical monitor.
 
 |
|------------------------------------------------------------------------------------------------------------------------------|--------------------------------------------------------------------------------------------------------------------------------------------------------------------------------------------------------------------------------------------------------------------------------------------------------------------------------------------------------------------------------------------------------------------------------------------------------------------------------------------------------------------------------------------------------------------------------------------------------------------------------------------------------------------------------------------------------------------------------------------------------------------------------|

IV: intravenous; BAL: bronchoalveolar lavage.

- If corticosteroids have been initiated, they must be tapered over  $\geq 1$  month to  $\leq 10$  mg/day oral prednisone or equivalent before pembrolizumab can be resumed. Add prophylactic antibiotics for opportunistic infections.
- The acceptable length of the extended period of time for which pembrolizumab can be held to allow for corticosteroids to be reduced to  $\leq 10$  mg/day oral prednisone or equivalent must be agreed upon by the investigator and the Medical Monitor.

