|-----------------------------------------------------------------------------------------------------------------------------------------|-------------------------------------------------------------------------------------------------------------------------------------------------------------------------------------------------------------------------------------------------------------------------------------------------------------------------------------------------------------------------------------------------------------------------------------------------------------------------------------------------------------------------------------------------------------------------------------------------------------------------------------------------------------------------------------------------------------------------------------------|
|                                                                                                                                         | 
 
Initiate treatment with 1–2 mg/kg/day prednisone or equivalenta
 
Monitor participants for signs and symptoms of enterocolitis (ie, diarrhea, abdominal pain, blood or mucus in stool with or without fever) and of bowel perforation (ie, peritoneal signs and ileus)
 
If event resolves to Grade 1 or better within 2 weeks, resume evorpacept (ALX148, reduced by one level), cetuximab (dose determined by institutional guidelines), and pembrolizumab (fixed dose), unless otherwise agreed between the Investigator and medical monitor. If not, permanently discontinue study treatments.a- c
 
                                              |

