| 
Colitis, grade 3: Severe abdominal pain; peritoneal signs
                                                                      | 
 
Hold evorpacept (ALX148), cetuximab, and pembrolizumab
 
Initiate supportive care and monitor patient closely.
 
Discontinue medications that may exacerbate colitis (e.g., NSAIDs).
 
Refer patient to gastrointestinal specialist for evaluation and confirmatory biopsy.
 
Monitor participants for signs and symptoms of enterocolitis (ie, diarrhea, abdominal pain, blood or mucus in stool with or without fever) and of bowel perforation (ie, peritoneal signs and ileus)
 
Initiate treatment with 1-2 mg/kg/day IV methylprednisolone or equivalent and convert to 1-2 mg/kg/day oral prednisone or equivalent upon improvement.
 
If event resolves to Grade 1 or better within 2 weeks (unless otherwise agreed between the Investigator and medical monitor), resume evorpacept (ALX148, reduced by one dose level) and cetuximab (dose determined by institutional guidelines). Pembrolizumab may be resumed at fixed dose after discussion with the medical monitor.a-c
 
 |
| 
Colitis, grade 3 (recurrent) or grade 4:
 
Colitis, grade 4: Life-threatening consequences; urgent intervention indicated
 | 
 
Permanently discontinue study treatments and contact Medical Monitor.
 
Initiate supportive care and monitor patient closely.
 
Discontinue medications that may exacerbate colitis (e.g., NSAIDs).
 
Refer patient to GI specialist for evaluation and confirmatory biopsy.
 
Monitor participants for signs and symptoms of enterocolitis (ie, diarrhea, abdominal pain, blood or mucus in stool with or without fever) and of bowel perforation (ie, peritoneal signs and ileus)
 
Initiate treatment with 1-2 mg/kg/day IV methylprednisolone or equivalent and convert to 1-2 mg/kg/day oral prednisone or equivalent upon improvement.
 
If event does not improve within 48 hours after initiating corticosteroids, consider adding an immunosuppressive agent.
 
If event resolves to Grade 1 or better, taper corticosteroids over <math>\geq 1</math> month.
 
                                                                                                                      |

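### For Grade 3/4 immune pneumonitis the protocol gives two starting steroid routes: IV in Section 12.1.1, oral in the Section 12.1.7 table, with nothing to say which governs

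*Protocol*

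**What the plan says.** Section 12.1.1 of the protocol (Appendix 1) gives general rules for immune-related adverse events. On steroid route it says "Severe and life-threatening irAEs should be treated with IV corticosteroids followed by oral steroids". The line introducing those rules adds that "additional details are provided in Sections 12.1.3 through 12.1.11".

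Section 12.1.7 then tabulates pneumonitis by grade. Grades 3 and 4 are joined by *OR* and share one guidance cell. Their labels are "Grade 3 (Severe symptoms; limiting self care ADL; oxygen indicated" and "Grade 4 (Life-threatening respiratory compromise; urgent intervention indicated (e.g., tracheotomy or intubation". The steroid instruction in that cell is "If bronchoscopy is consistent with immune-related etiology, initiate treatment with 1–2 mg/kg/day oral prednisone or equivalent", and the next step is "If pulmonary event does not improve within 48 hr or worsens, consider adding an immunosuppressive agent".

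The Grade 2 row carries the same steroid sentence, word for word.

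**The concern.** A clinician treating immune pneumonitis in a patient on oxygen or a ventilator finds an IV start in the general rule and an oral start in the organ-specific table. The table is what a site will most likely consult at the bedside, and it names the weaker instruction for the sicker patient.

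The identical Grade 2 sentence suggests text carried down the table rather than a deliberate exception.

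The event is foreseeable. Section 12.1.7 reports pneumonitis with both pembrolizumab and cetuximab. Section 2.3.1 gives it as the most common event leading to pembrolizumab discontinuation in both pooled safety datasets (1.2% and 1.5%).

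**Working it through.** There is no figure to recompute. The check is a comparison of text and a count of rows.

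**1. Do both instructions apply to the same patient?** Yes. The severity table in Section 12.1.1 describes Grade 3 as severe and Grade 4 as life-threatening, and the pneumonitis labels use the same terms. The steroid step in the row applies only if bronchoscopy points to an immune cause, so any patient who reaches it has an immune-related event of the kind the general rule covers.

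**2. Does the row escalate from Grade 2?** The study-drug steps do; the steroid start does not.

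| Step in Section 12.1.7 | Grade 2 | Grade 3 or 4 |
|---|---|---|
| Evorpacept | may continue at investigator discretion | held |
| Pembrolizumab and cetuximab | withheld | permanently stopped |
| Steroid start if immune cause supported | oral prednisone or equivalent, 1–2 mg/kg/day | the same sentence |
| No improvement within 48 hours, or worsening | no such step | consider adding an immunosuppressant; no move to IV steroid |

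**3. Does any text rank the two instructions?** No.
- The introduction to the general rules calls the later sections a source of further detail. It does not say they replace the route.
- The one exception clause in Section 12.1.1 that defers to the later sections concerns when study drugs are interrupted, not steroid route.
- Footnotes a to c of the pneumonitis table deal with tapering and with restarting pembrolizumab.

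**4. One row, or a pattern?** All Grade 3 and/or 4 rows in Sections 12.1.3 to 12.1.12 that name a systemic steroid:

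| Instruction | Rows | Count |
|---|---|---|
| IV start named | hemolysis Grade 4; colitis Grade 3; colitis recurrent Grade 3 or Grade 4 | 3 |
| Oral or IV, by symptoms or speed of onset | hemolysis Grade 3 | 1 |
| No route named | diarrhea intolerable Grade 2 or Grade 3; diarrhea recurrent Grade 3 or Grade 4; hypophysitis Grade 3/4; nephritis Grade 3/4; hemophagocytic lymphohistiocytosis Grade 3/4 | 5 |
| *Consider* oral, events of mixed cause | non-acneiform rash Grade 3; hepatotoxicity Grade 3; hepatotoxicity Grade 4 | 3 |
| Oral start directed once an immune cause is supported | pneumonitis Grade 3/4 | 1 |

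Total: 3 + 1 + 5 + 3 + 1 = 13.

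Acneiform rash is left out because its steroid is topical, and infusion reaction because it has no steroid step by grade. The rows with no route, such as the diarrhea rows ("Initiate treatment with 1–2 mg/kg/day prednisone or equivalent"), leave the general rule free to supply it. The *consider* rows do not direct a start. Only the pneumonitis row both directs treatment and names a different first route.

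**The case against.** The strongest reply is that both instructions can be followed together. The row says *or equivalent*; Section 12.1.1 supplies the route and says the tables add detail. Read that way, the patient starts IV at a dose equivalent to 1–2 mg/kg/day of prednisone and later moves to oral. The appendix is framed as guidelines, tells investigators to use medical judgment, and in this row refers the patient to pulmonary and infectious disease specialists. Nothing forces an oral start in an intubated patient.

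This stands in part: an IV start is permitted. But permission is weaker than the direction in Section 12.1.1. Elsewhere the appendix is explicit when it wants IV or a free choice: the Grade 3 hemolysis row offers either route, and the colitis rows name IV methylprednisolone. If instead the specific row is taken to prevail, the named start for a ventilated patient is oral, and the row still needs correcting.

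A second reply is that hepatotoxicity Grades 3 and 4 also name oral prednisone, so the one-row count depends on how rows are classified. Those rows are in some tension with the general rule. They differ because they say *consider* and cover enzyme or bilirubin rises of any cause, whereas the pneumonitis step begins only after an immune cause is supported.

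A third reply is that considering an immunosuppressant at 48 hours is ordinary practice within this appendix: it follows the general rule on events that steroids do not control, and the most severe colitis row has the same step. That is right. The step is not itself a fault; it only shows that the row never reaches IV steroid.

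**Conclusion.** The inconsistency is real and limited to one row of 13. For immune pneumonitis of Grade 3 or 4, Section 12.1.1 directs IV then oral steroids, Section 12.1.7 directs an oral start, and the protocol does not say which applies. It should be corrected because it is a stated instruction for severe and life-threatening toxicity. It has no bearing on endpoints, analysis or sample size.

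The conclusion rests on reading *severe* in Section 12.1.1 as Grade 3, as its own severity table does, and on Grades 3 and 4 sharing one guidance cell, as the table layout shows. The protocol gives no expected rate of Grade 3/4 pneumonitis on this combination and no outcome difference between an oral and an IV start, so the clinical consequence cannot be quantified from the document.

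**What to change.** In the Grade 3/4 row of Section 12.1.7, keep the bronchoscopy condition and replace the steroid instruction with the wording Section 12.1.8 uses for Grade 3 and 4 colitis: "Initiate treatment with 1-2 mg/kg/day IV methylprednisolone or equivalent and convert to 1-2 mg/kg/day oral prednisone or equivalent upon improvement". Leave the Grade 2 row as it is.

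One consequence should be settled at the same time. The table sends recurrent Grade 1 and Grade 2 pneumonitis to this row, so those patients would also be directed to an IV start. If that is not intended, the row should say so.

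A sentence in Section 12.1.1 on whether the general rule or the table decides steroid route would be a useful addition. It would not replace the row edit if the tables were given precedence.

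The cost is a wording change to one line of one appendix row, with no effect on data collection or sample size.

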b. Examples of self-care activities of daily living include bathing, dressing and undressing, feeding oneself, using the toilet, and taking medications, as performed by patients who are not bedridden.

c. If an event is assessed as a "significant medical event," it must be reported as a serious adverse event.

AEs associated with pembrolizumab exposure, including coadministration with additional compounds, may represent an immunologic etiology. These immune-related AEs (irAEs) may occur shortly after the first dose or several months after the last dose of pembrolizumab/combination treatment and may affect more than one body system simultaneously. Therefore, early recognition and initiation of treatment is critical to reduce complications. Based on existing clinical study data, most irAEs were reversible and could be managed with interruptions of pembrolizumab/combination treatment, administration of corticosteroids and/or other supportive care. For suspected irAEs, ensure adequate evaluation to confirm etiology or exclude other causes. Additional procedures or tests such as bronchoscopy,

endoscopy, skin biopsy may be included as part of the evaluation. Dose modification and toxicity management guidelines for irAEs are provided in Section 12.1 subsections.

AEs should be managed with maximal supportive care per Investigator discretion and based on published guidelines, taking the most likely causative drug into account. In general, no specific dose adjustments or changes to the dose schedule are recommended for Grade 1/2 treatment-related toxicity with several exceptions noted in Sections 12.1.3 through 12.1.9. However, Investigators should always manage their patients according to their medical judgment based on the particular clinical circumstances and utilize the following guidelines.

When study interventions are administered in combination, attribution of an adverse event to a single or multiple compound(s) is likely to be difficult. Therefore, evorpacept (ALX148), cetuximab, **and** pembrolizumab should be interrupted for Grade  $\geq 3$  treatment-related toxicity, unless as otherwise described in Sections 12.1.3 through 12.1.11. Retreatment following treatment interruption for treatment-related toxicity or the start of a new cycle of treatment may begin only if (and as detailed in Sections 12.1.3 through 12.1.11):

- ANC  $\geq 1,000/\text{mm}^3$
- Platelet count  $\geq 50,000/\text{mm}^3$

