- Treatment may be resumed when toxicities have returned to baseline or Grade  $\leq 1$  severity (or, at the Investigator discretion, Grade  $\leq 2$  if not considered a safety risk for the patient). A treatment delay of more than 14 days (beyond the next scheduled study drug infusion) due to lack of recovery will result in discontinuation of the patient from the treatment unless otherwise agreed between the Investigator and AGICC.
- Upon resuming:
  - Evorpaccept (ALX148) should be reduced by one dose level (Section 12.1.2)
  - Cetuximab and pembrolizumab can be continued at the same dose level (Section 12.1.2). Cetuximab dose may be reduced (Section 12.1.2) per Investigator discretion
  - If a pembrolizumab immune-mediated toxicity is suspected, guidelines for workup and management should be followed. If severe, pembrolizumab can be discontinued per investigator discretion (must discontinue if grade 4 or recurrent grade 3 and likely discontinue if grade 3)

If the AE that led to treatment interruption improves to allow treatment resumption/resolves, then re-dosing in that cycle is allowed. Doses omitted for toxicity are not replaced within the same cycle. If a treatment interruption continues beyond Day 21 of the current cycle, then the day when treatment is restarted will be counted as Day 1 of the next cycle. A treatment delay of more than 14 days (beyond the next scheduled study drug infusion) due to lack of recovery will result in discontinuation of the patient from the treatment unless otherwise agreed between the Investigator and AGICC.

Evorpaccept (ALX148), cetuximab, and pembrolizumab may be interrupted for situations other than treatment-related AEs such as medical / surgical events and/or unforeseen circumstances not related to study intervention. However, intervention is to be restarted within 3 weeks of the originally scheduled dose, unless otherwise discussed with AGICC. The reason for study intervention interruption is to be documented in the patient's study record.

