| 
New-onset type I diabetes mellitus or grade 3 or 4 hyperglycemia associated with evidence of <math>\beta</math>-cell failure
 
Grade 3 hyperglycemia: Insulin therapy initiated; hospitalization indicated
 
Grade 4 hyperglycemia: Life-threatening consequences; urgent intervention indicated
 | 
 
Withhold evorpacept (ALX148), cetuximab, and pembrolizumab
 
Initiate insulin replacement therapy for participants with type I diabetes mellitus
 
Administer antihyperglycemic in participants with hyperglycemia
 
Monitor participants for hyperglycemia or other signs and symptoms of diabetes
 
Evorpacept (ALX148), cetuximab, and pembrolizumab can be resumed when the event improves to <math>\leq</math>Grade 1 or baseline
 
 |
| 
Hypophysitis grade 2: Moderate; minimal, local or noninvasive intervention indicated; limiting age-appropriate instrumental ADL
                                                                                                                                                                            | 
 
Hold pembrolizumab
 
Continue or hold evorpacept (ALX148) and cetuximab at Investigator's discretion
 
Administer corticosteroids and initiate hormonal replacements as clinically indicated
 
Monitor for signs and symptoms of hypophysitis (including hypopituitarism and adrenal insufficiency)
 
                                                                                                                                           |
| 
Hypophysitis, grade 3 or 4
 
Hypophysitis, grade 3: Severe or medically significant but not immediately life-threatening; hospitalization or
                                                                                                                                                          | 
 
Hold evorpacept (ALX148), cetuximab, and pembrolizumab
 
Administer corticosteroids and initiate hormonal replacements as clinically indicated
 
Monitor for signs and symptoms of hypophysitis
 
                                                                                                                                                                                                                                                      |

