|                                                                                                                                                                                                                                        |                                                                                                                                                                                                                                                                                                                                                                                                                                                                                                                                                              |
|----------------------------------------------------------------------------------------------------------------------------------------------------------------------------------------------------------------------------------------|--------------------------------------------------------------------------------------------------------------------------------------------------------------------------------------------------------------------------------------------------------------------------------------------------------------------------------------------------------------------------------------------------------------------------------------------------------------------------------------------------------------------------------------------------------------|
| prolongation of existing hospitalization indicated; limiting self care ADL

Hypophysitis, grade 4: Life-threatening consequences; urgent intervention indicated                                                                  | (including hypopituitarism and adrenal insufficiency)

• If event improves to <math>\leq</math>Grade 1 or baseline, resume evorpacept (ALX148), cetuximab, and pembrolizumab after discussion with the medical monitor. Pembrolizumab can be permanently discontinued at the discretion of the investigator and medical monitor.

                                                                                                                                                                           |

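### Section 12.1.1 requires permanent pembrolizumab discontinuation after any other grade 4 immune-related event, but three endocrine rows of Section 12.1.10 allow restart at grade 4, and no clause says which rule governs

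*Protocol*

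**What the plan says.** Section 12.1.1 (General Guidance) lists instructions for immune-related adverse events. One bullet makes permanent discontinuation of pembrolizumab mandatory for certain neurologic, cardiac and severe skin events "and other grade 4 or recurrent grade 3 immune-related adverse events". It names no endocrine exception. A related parenthetical further down the section reads "must discontinue if grade 4 or recurrent grade 3 and likely discontinue if grade 3". That parenthetical sits in the branch for toxicity judged unlikely to be due to cetuximab or pembrolizumab, in a sub-bullet on suspected pembrolizumab immune-mediated toxicity.

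A separate bullet governs restart after a hold: "If pembrolizumab has been withheld, pembrolizumab may resume after the irAE decreases to" grade 1 or lower, with a limit on the steroid dose.

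Section 12.1.10 (Management of Endocrine Toxicity) has three rows that reach grade 4 and allow restart:

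- New-onset type 1 diabetes, or grade 3 or 4 hyperglycemia with beta-cell failure: "Evorpacept (ALX148), cetuximab, and pembrolizumab can be resumed when the event improves to" grade 1 or below, or baseline.
- Hypophysitis grade 3 or 4: once the event is at or below "Grade 1 or baseline, resume evorpacept (ALX148), cetuximab, and pembrolizumab after discussion with the medical monitor". The row adds "Pembrolizumab can be permanently discontinued at the discretion of the investigator and medical monitor".
- Hyperthyroidism grade 3 or 4: the same restart and discretion wording, but from grade 2 or below, or baseline.

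**The concern.** A patient has grade 4 hypophysitis, which the row itself defines as life-threatening, and then improves to grade 1. Section 12.1.10 lets the investigator restart pembrolizumab after speaking to the medical monitor. Section 12.1.1 forbids that restart. Both passages are in force in the same appendix.

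At stake is re-exposure to a checkpoint inhibitor after a life-threatening immune-related event. Section 5.5 foresees about 5 sites. One could restart under the table while another treats the same restart as prohibited, and a monitor could record the first as a deviation under Section 10.1.9. Section 4.1.3 records a grade 5 hemophagocytic lymphohistiocytosis in Stage 1, assessed as possibly related to all three drugs, so stopping rules in this trial should leave no doubt.

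**Working it through.** No figure in the plan depends on this, so the check is a comparison of texts.

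**Step 1. Does the mandatory rule cover these events?** It applies to other immune-related events of grade 4. The closing line of Section 12.1.10 speaks of additional endocrine immune-related events, which implies that the tabulated ones are immune-related too. Section 2.3.1 lists type 1 diabetes, hypophysitis and hyperthyroidism among pembrolizumab's adverse events of special interest. The rule therefore covers them.

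**Step 2. Compare the endocrine rows that reach grade 4.**

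| Row of 12.1.10 | Pembrolizumab under 12.1.1 at grade 4 | Pembrolizumab under 12.1.10 | Medical monitor named in the row's restart step | Conflict |
|---|---|---|---|---|
| Type 1 diabetes, or grade 3 or 4 hyperglycemia | Permanent stop | May resume at grade 1 or below, or baseline | No | Yes |
| Hypophysitis grade 3 or 4 | Permanent stop | Resume at grade 1 or below, or baseline; stopping discretionary | Yes | Yes |
| Hyperthyroidism grade 3 or 4 | Permanent stop | Resume at grade 2 or below, or baseline; stopping discretionary | Yes | Yes |
| Hypothyroidism grade 3 or 4 | Permanent stop | Permanent stop | Not applicable | No |

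Four rows reach grade 4. Three conflict with Section 12.1.1 and one agrees with it.

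**Step 3. Does any clause give the table precedence?** Three phrases in Section 12.1.1 point to the later sections.

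- "unless as otherwise described in Sections 12.1.3 through 12.1.11" qualifies the instruction to interrupt all three drugs for treatment-related toxicity of grade 3 or higher. It does not reach permanent discontinuation.
- Retreatment "may begin only if (and as detailed in Sections 12.1.3 through 12.1.11") sets conditions that must be met before dosing resumes. It does not authorize retreatment where a stop is mandatory.
- The heading of the immune-related list promises additional details in the later sections. More detail on a mandatory rule does not suspend it.

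**Step 4. Can an endocrine exception be inferred from the pattern?** Section 12.1.10 itself requires permanent discontinuation for hypothyroidism grade 3 or 4, so the section applies no uniform exception. Elsewhere in Appendix 1, the grade 4 rows for non-acneiform rash, hepatotoxicity, pneumonitis, diarrhea, colitis, nephritis and hemophagocytic lymphohistiocytosis all stop pembrolizumab permanently. The three endocrine rows are outliers, and nothing says whether that was intended.

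**Step 5. Recurrent grade 3.** None of the three rows mentions recurrence. A site can follow the row for a first grade 3 event and Section 12.1.1 for a recurrence without breaching either. The diarrhea and colitis tables in Section 12.1.8 do give recurrent grade 3 its own entry, so the silence here is an ambiguity, but it is not a contradiction.

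**Step 6. The hyperthyroidism restart threshold.** Grade 2 or below departs from the grade 1 limit in the immune-related restart bullet. However, Section 12.1.1 twice allows restart at grade 2 at investigator discretion: in the general non-hematologic retreatment criterion and in the branch for toxicity attributed to evorpacept. The mismatch already exists within Section 12.1.1, so this is secondary.

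**The case against.** The strongest reply is that the specific governs the general. The mandatory bullet stands under General Guidance, in a list of general instructions, and Section 12.1.1 says that the later sections give specific guidelines. Those sections do set event-specific outcomes: grade 3 hepatotoxicity and grade 3 hypothyroidism lead to permanent pembrolizumab discontinuation, where the general restart bullet would let a first grade 3 event resume. On that reading the endocrine rows are deliberate tailoring.

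This shows that tailoring is plausible. It does not remove the conflict. In both examples the table is stricter than a permissive default, so following the table breaches nothing in Section 12.1.1. The endocrine rows go the other way and relax a mandatory stop, and no text says that they may.

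A second reply concerns impact. In two of the three rows restart follows discussion with the medical monitor, which gives a chance to catch inconsistent decisions. That is a fair limit, but the diabetes row has no such step, and a discussion does not waive a mandatory rule. It is also true that a site that stops pembrolizumab complies with both sections; the problem arises only on restart.

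A reader might go further and count recurrent grade 3 as a second trigger in each row (3 × 2 = 6), then add the hyperthyroidism threshold for 7. The documents do not support that count, for the reasons in steps 5 and 6. Nor is the later parenthetical a free-standing second statement of the rule, since it belongs to the branch for toxicity judged unlikely to be due to cetuximab or pembrolizumab. The mandatory bullet alone establishes the point.

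**Conclusion.** The contradiction is real and limited: three rows, one trigger (grade 4), three explicit conflicts. Recurrent grade 3 is at most an ambiguity, and the hyperthyroidism threshold is a secondary mismatch. The conclusion rests on the tabulated endocrine events being immune-related, which the protocol's own wording supports, and on the absence of any precedence clause. The count measures conflicts in the text, not risk; the protocol gives no rates for these events under this regimen, so the number of patients affected cannot be estimated. Sample size, power and alpha are untouched. It should be corrected because it leaves a patient-safety stopping rule open to opposite readings.

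**What to change.** Either of two changes resolves the grade 4 conflict. The clinical choice is the sponsor's.

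(a) Add to the mandatory discontinuation bullet in Section 12.1.1, and for consistency to the later parenthetical, an exception for endocrine events managed as specified in Section 12.1.10. Keep the mandatory stop for hypothyroidism grade 3 or 4, and state whether recurrent grade 3 falls within the exception. Naming the three events would be tighter, because the last line of Section 12.1.10 leaves unlisted endocrine events to standard protocols and a broad phrase could cover those too. Cost: one phrase at two points and one clarifying sentence.

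(b) Amend the three rows of Section 12.1.10 to require permanent pembrolizumab discontinuation at grade 4, leaving restart available at grade 3. Cost: three row edits.

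The same amendment could align the hyperthyroidism restart threshold with the grade 1 bullet or except it expressly. Neither option changes data collection or analysis.
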